#### Peripheral muscle strength

Peripheral muscle strength will be measured by handgrip strength (HGS) with a hand-held dynamometer (model SH 5001, brand SAEHAN), respecting the protocol recommended by the American Association of Hand Therapists (ASHT). Participants are going to be guided to remain seated, with the shoulder in a neutral position, one hand resting on the thigh and the elbow of the member that will be measured must remain flexed at 90 degrees, with the forearm in neutral rotation [17]. The interval between attempts will be one minute. The dominant hand will be used and the best score between the three measures is going to be considered a handgrip strength measure.

#### Functional capacity

Functional capacity is defined as the ability to perform activities of daily living (ADL) with autonomy [18, 19]. In this study, it will be evaluated with the one-minute sit-to-stand test, the Barthel index, the Katz index, and the Lawton-Brody scale.

One-minute sit-to-stand test will be based on a protocol described by Ozalevli and cols [20]. With the hands on the hip, participants will be guided to sit and stand completely in a chair (height 46 centimeters) as often as possible during 1 minute.

Katz index will be used to evaluate basic ADL. This index covers self-care, including feeding, bathing, dressing, toileting, transferring, and continence, with scores ranging from 0 (independent) and 1 (dependent) for each item [21, 22]. As a result, participants will be classified from 0 (independency for ADL) to 6 (total dependency for ADL) [21, 22].

The Barthel index evaluates the autonomy for self-care, in addition to mobility [23–25]. It is a tool that covers 10 tasks: feeding, bathing, grooming, dressing, bowels, bladder, toilet use, transfers (bed to chair and back), mobility (on level surfaces), and stairs [23–25]. The final score ranges from 0 to 100 and each item is scored according to how the individual performs each task (independently, with some help, or dependently). The higher the score, the higher the independency: 80 to 100 indicate independence; 60–79 points for slight dependency; 40–59 points for moderate independence; 20–39 points for severe dependency; 0–20 points for total dependency [23–25].

Instrumental ADL will be evaluated by the Lawton-Brody scale, which includes seven activities: the ability to use the telephone, mode of transportation, shopping, housekeeping, food preparation, responsibility for own medications, and ability to handle finances [26]. Each item has three possible answers: independent (3 points), need help (2 points), and unable to perform the task (1 point) [26]. The final score classifies the individuals as independent (21 points), partially dependent (8–21 points), or totally dependent (7 points) [27].

#### Quality of life

Quality of life will be evaluated by Euro Quality of Life Instrument-5D (EQ-5D) [28]. This instrument covers five health dimensions: mobility, self-care, usual activities, pain/discomfort, and anxiety/depression [29]. Each dimension is classified into 3 levels: no problems (1 point), some problems (2 points), and extreme problems (3 points) [30]. The results will be presented as frequency distributions of levels and dimensions over time, including changes within dimensions [29].

#### Fear of falling

Fear of falling will be evaluated by Falls Efficacy Scale International (FES-I) [31]. This tool has 16 items that evaluate, for example, walking on a slippery surface or an uneven surface, visiting a friend/relative, or attending a social event [32]. The fear of falling in each activity is classified on a 4-point scale (1—not at all concerned to 4—very concerned) [32]. The total score ranges from 16 to 64: 16–22 (low concern), 20–27 (moderate concern), and 28–64 (high concern) [32].

#### Fall history

Fall is a sudden and involuntary transfer of the body to the ground or a lower level [33]. Fall history will be evaluated periodically during the study and the patients must fill out a diary to register every moment in which they fall, and at the end of the study, this data (including location, associated injuries, need for special care after the fall) and the total number of falls will be evaluated.

#### Cognition and mood assessment

Cognitive assessment will be performed using the 10-Point Cognitive Screener (10-CS), a tool that consists of a brief cognitive screening, easily applicable and with greater accuracy and advantages [34]. It covers an evaluation of temporal orientation (1 point), verbal fluency (0 to 4 points), and three-word recall (1 point for each word) [34]. In the end, the score is adjusted for the education degree, adding 2 points for illiterate and 1 point for individuals with 1 to 3 years of education. Results are interpreted as follows: ≥ 8 points–normality, 6 to 7 points—possible cognitive impairment (usually mild cognitive impairment), and, 0 to 5 points—probable cognitive impairment (usually dementia) [34].

Assessment of mood disorders will be evaluated by the Geriatric Depression Scale (GDS-15) [35], which consists of 15 items (possible answers Yes or No) and a score of 0 or 1. The final score greater or equal to 5 points indicates the presence of significant symptoms of depression [35].

#### Geriatric vulnerability and frailty assessment

Geriatric vulnerability will be evaluated by the PRO-AGE scoring system, a fast tool developed to assess older patients in the ED [36]. Variables include functional impairment, recent hospitalization, advanced age, acute mental change, weight loss, male sex and fatigue.

Frailty will be evaluated using the Clinical Frailty Scale (CFS), which summarises the level of fitness or frailty of an older adult after evaluation by a health care professional [37]. Patients will be classified in one of the following categories: 1- very fit; 2- well; 3- managing well; 4- vulnerable; 5- mildly frail; 6- moderately frail; 7- severely frail; 8- very severely frail; 9- terminally ill [38].

#### Medication assessment

Medications used by patients will be tabulated with a detailed description including active ingredients, presentation, dose, and frequency. They will also be classified according to Beers criteria for potentially inappropriate medication use in older adults [39]. This criterion is categorized as 1) medications considered as potentially inappropriate; 2) medications potentially inappropriate in patients with certain diseases or syndromes; 3) medications to be used with caution; 4) potentially inappropriate drug–drug interactions; 5) Medications whose dosages should be adjusted based on renal function [39].

### Interventions

The interventions will be performed according to the randomization after the baseline data collection.

#### Training of walking aids

Training will be carried out with patients from groups WA and WAT. A physical therapist will identify the mobility needs and will indicate the most appropriate walking aid (cane or walker) considering the following parameters.

Canes: one upper limb used for a walk, light weight-bearing and need for somatosensorial feedback; the cane must be positioned between 15 and 20 centimeters laterally to the feet; the patient’s hand should be supported on the cane at the height of the greater trochanter of the femur and the elbow should be flexed approximately by 30°; in general, the cane is used on the opposite side of the injured leg.Walkers: both upper limbs used to walk, heavy weight bearing, and presence of postural instability; the equipment must be held between 20 and 25 centimeters in front of the body with relaxed shoulders, erect torso, and elbow flexed at 20° to 30°; during the total weight-bearing gait, the walker should be lifted and move forward approximately arm’s length, while one lower limb move forward followed by the other, and the cycle repeats; in a non-weight bearing gait, the walker is lifted and moves forward, then the weight is transferred to the walker through the upper limbs, the affected limb is held in a position anterior to the person’s body, but does not contact the ground, the unaffected limb is moved forward and this cycle repeats.

#### Telemonitoring

Follow-up will be carried out only in the WAT group. Telemonitoring will occur every two weeks for three months after the ED discharge, through video call (about 15 minutes). On these opportunities, the importance of using mobile devices and the guidance on safe gait will be reinforced.

#### Guidance on safe gait

Guidance on safe gait will be carried out for all the groups in the study. Subjects will be instructed on strategies for fall prevention [40] and will receive a printed leaflet summarizing it (S2 File).

### Outcomes

#### Primary outcome

The primary outcome will be fear of falling.

#### Secondary outcomes

Secondary outcomes will include mobility, functionality, quality of life, mood, cognition, and occurrence of falls in three months.

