Finally, new technologies have been developed to improve health care, including telemonitoring. Telemonitoring is defined as the use of information technology and telecommunications for remote health care [9] and its main advantages are reducing unnecessary visits and home visits, reducing the risk of infections, monitoring the rehabilitation process, and improving patient compliance [10]. However, most studies related to telemonitoring are carried out with patients who have chronic diseases. Also, there are no data on the effects of an intervention encompassing gait devices, associated or not with telemonitoring, to improve the mobility of older patients admitted to the ED despite recommendations from international societies and the Geriatric Emergency Department Accreditation (GEDA) accreditation [3].

The hypothesis of the study is that the provision of walking aids enhances mobility in living spaces and will have a significant impact on fear of falling, functionality, and quality of life. Therefore, this study aims to evaluate the efficacy of a program of training and provision of walking aids, associated or not with telemonitoring, on fear falling, mobility, quality of life, and risk of falls up to 3 and 6 months in older adults cared for in an ED. In addition, we hypothesize that fear of falling may be correlated with lower scores in mobility, quality of life, and risk of falls.

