#### Assessment moments

Baseline assessment will be carried out before randomization and interventions. Assessment of gait speed and fear of falling will be repeated immediately after the intervention. Fear of falling, life-space mobility, functionality, quality of life, fall history, cognition and mood assessments will be repeated 3 and 6 months after intervention by a telephone interview or video call.

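### The fall outcome has no single window or measure, and the between-group tests named neither cover a yes/no outcome nor allow for unequal follow-up

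*Protocol article*

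**What the plan says.** All references are to the protocol article.

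- Secondary outcomes: "Secondary outcomes will include mobility, functionality, quality of life, mood, cognition, and occurrence of falls in three months".
- Fall history: participants keep a fall diary. The section names what is to be assessed: "at the end of the study, this data (including location, associated injuries, need for special care after the fall) and the total number of falls". Falls are also to be assessed periodically, without naming the contacts.
- Introduction (aim; the Abstract has a near-identical sentence): "risk of falls up to 3 and 6 months in older adults cared for in an ED".
- Assessment moments: "fall history, cognition and mood assessments will be repeated 3 and 6 months after intervention by a telephone interview or video call". This applies to all arms.
- Statistical analysis: between-group comparisons use one-way ANOVA or Kruskal-Wallis. The Timed Up and Go test before and after the intervention is the only variable given a different test. Categorical data are to be shown as absolute and relative numbers. The time points are baseline, 3 and 6 months.
- Sample: 20% loss to follow-up is expected, with 51 randomised per group.
- Telemonitoring: "Telemonitoring will occur every two weeks for three months after the ED discharge". Only the walking aid with telemonitoring (WAT) group receives it. The Discussion suggests that telemonitoring could reduce loss to follow-up.

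**The concern.** Falls are part of the study's stated aim, yet the article describes the fall endpoint in ways that do not agree. The outcome list has a yes/no event over 3 months, the instrument section has a count to study end, and the aim has a risk at two horizons. These are different quantities, not a shorter and a longer description of one quantity. If they are not reconciled before the data are seen, the reported fall result can be picked from several.

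The analysis section does not settle the matter. It names no between-group test for a yes/no outcome. For a count, the tests it names treat a participant followed for six weeks like one followed for six months. That matters more than usual here, because only one arm gets regular contact that may keep its members in the study longer.

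**Working it through.** The article gives no fall rate, effect size or power for falls, so there is no figure to reproduce. The sample size rests on FES-I alone.

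**1. The sections side by side.**

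| Section | Measure | Window |
|---|---|---|
| Secondary outcomes | occurrence | 3 months |
| Fall history | total number, with details | end of study (last assessment is at 6 months) |
| Introduction | risk | 3 and 6 months |
| Assessment moments | fall history | 3 and 6 months |
| Statistical analysis | none specific to falls | baseline, 3 and 6 months |

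Two measures by two windows give 2 × 2 = 4 candidate results. With each tested at 5%, the chance of at least one false positive lies between 5% (if they always agree) and 4 × 5% = 20% (upper bound). The results are strongly correlated, so the true value is well below that bound.

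**2. Do the windows differ materially?** Assume negative binomial counts with mean μ and dispersion k. Then P(at least one fall) = 1 − (1 + kμ)^(−1/k). Assumed inputs: 0.25 or 0.5 falls per 3 months, twice that at 6 months, and k = 1 or 2.

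- 0.25 per 3 months, k = 1: 20.0% at 3 months, 33.3% at 6 months.
- 0.5 per 3 months, k = 1: 33.3% and 50.0%.
- 0.25 per 3 months, k = 2: 18.4% and 29.3%.
- 0.5 per 3 months, k = 2: 29.3% and 42.3%.

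**3. Precision by window.** For two arms of 41 (51 × 0.8 = 40.8), SE of the log rate ratio = √[2(1/μ + k)/41]. At 0.25 falls per 3 months:

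- k = 0: √(8/41) = 0.44 at 3 months and √(4/41) = 0.31 at 6 months, 29% smaller.
- k = 1: √(10/41) = 0.49 and √(6/41) = 0.38, 23% smaller.
- k = 2: √(12/41) = 0.54 and √(8/41) = 0.44, 18% smaller.

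**4. Unequal follow-up.** Let L be the fraction lost and t the mean fraction of the window observed among those lost. Observed time per person randomised is 1 − L(1 − t). Assume equal true rates, and that the falls recorded for lost participants enter the total as they stand. If the other arms lose the planned 20% and WAT loses none, the raw WAT-to-other ratio of mean counts is 1/(1 − 0.20 × 0.5) = 1.11 for t = 0.5, and 1/(1 − 0.20) = 1.25 for t = 0. With equal loss it is 1.00. A follow-up offset brings the ratio back to 1 if loss is unrelated to falling.

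**5. Do the named tests misbehave on complete counts?** In 10,000 simulated trials per setting (41 per arm, the rates and dispersions of step 2, no true effect, 70% of falls detected in every arm), null rejection was 3.9-4.8% for ANOVA and 4.7-5.0% for Kruskal-Wallis. Both hold their level.

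**6. If the calls did raise detection in WAT (an assumption).** With 80% against 70% during months 0-3, the apparent rate ratio is 0.80/0.70 = 1.14 at 3 months and (0.80 + 0.70)/(2 × 0.70) = 1.07 at 6 months. With 95% against 70% it is 1.36 and 1.18. Null rejection was 4.4-5.8% and 5.9-10.3% respectively.

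**The case against.** The strongest reply is that this is a wording slip on one secondary outcome. The 6-month data are collected and evaluated anyway, a 3-month fall outcome matches the telemonitoring period and is defensible, and a condensed article may leave the falls model to an analysis plan not shown. Much of this stands. A 3-month endpoint would not throw away the later data, and either window could be chosen. What does not stand is leaving both open. An unseen plan may add a model, but it cannot make the published endpoint statements agree. Nor is the analysis text silent: it sets a general rule with a single exception, which is not falls. Kruskal-Wallis on a 0/1 coding would come close to a chi-square test, but the section does not assign it to categorical data, and it yields no effect estimate.

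A reader might go further and infer that falls are captured more fully in the WAT arm, so that the comparison is biased by arm. The article does not support this. The stated purpose of the calls is to reinforce device use and safe gait, and recording falls is not mentioned. The diary and the 3- and 6-month interviews are common to all arms, and post-intervention assessors are blinded. The calls might still prompt recall or diary entries, but that is a possibility and not a shown bias. A reader might also blame the tests themselves, but they keep their type I error on complete, equally recorded counts. Finally, the article does not say how the falls of participants lost early are handled, so step 4 shows what could happen and not what is planned.

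**Conclusion.** The point holds for the endpoint definition and for the fit of the stated analysis. Window and measure conflict within the article, which leaves four candidate results. Under the assumed rates, the share with any fall differs clearly by window (18-33% against 29-50%). The named tests do not cover a yes/no outcome and do not use follow-up time. With the planned 20% loss confined to the arms without telemonitoring, a raw count could show a WAT ratio between 1.11 and 1.25 with no true effect, and 1.00 if loss is equal. Rates, dispersion and loss pattern are assumptions.

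Differential recall or diary completion in the WAT arm should be noted when the 3-month result is interpreted, because the calls span exactly that window. It should not be reported as an established bias. Falls are a secondary outcome with no sample size attached, so the primary FES-I analysis is untouched.

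**What to change.** Reconcile the Introduction, Assessment moments, Fall history, Secondary outcomes and Statistical analysis sections to one prespecified fall measure and window. One workable choice is the number of falls from discharge to 6 months, with the 3-month result as supportive. Analyse it by negative binomial regression with log follow-up time as offset, adjusted for the fall history already collected at baseline, and report rate ratios with 95% confidence intervals.

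State that arm comparisons use only the diary and the 3- and 6-month interviews that all arms share. This keeps the recorded sources equal, but it does not remove recall or diary entries prompted by the calls, so that caveat belongs in the interpretation of the 3-month result.

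The cost is revised wording and a little more analysis work. No new data are needed. The change should be made before any unblinded data are seen.

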### Statistical analysis

Continuous variables will be expressed on average and standard deviation or median and interquartile interval 25%-75%. Categorical data will be presented in absolute and relative numbers. To verify the distribution normality of data, the Shapiro-Wilk normality test will be applied. For comparisons between groups over time, One-way ANOVA test for parametric data or Kruskall-Wallis for non-parametric data will be used. For intragroup analyses, repeated measures Analysis of Variance (RM-ANOVA) test for parametric data or Friedman test for non-parametric data will be used. Only for the Time Up and Go variable before and after intervention, a paired t-test will be used for parametric data, or a Wilcoxon test will be used for non-parametric data. For intergroup and intragroup analyses, the baseline, 3 and 6 months after discharge from the geriatric ED will be considered. To evaluate correlations, the Pearson correlation test will be used for parametric data and the Spearman test will be used for non-parametric data. All the analyses will be carried out using the Statistical Package for Social Sciences (SPSS) version 28.0.1 (SPSS Inc.^®^; Chicago, IL, USA), considering a significance level of 5%.

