### Sample

Sample size calculation was based on Morgan and cols study, which described a minimal detectable change (MDC_95_) of 8,2 points on Falls Efficacy Scale International (FES-I), with a standard deviation of 12 points [11]. For the calculation, ANOVA sample size was used, and three groups were considered. For an α of 0.05 and a power of 0.80, the total sample size was computed as 42 individuals. Due to the estimated loss of 20% during follow-up, the sample necessary for the success of the study was expanded to 153 individuals, 51 in each group (randomization 1:1:1).

We will include patients aged 65 years or older, admitted to the Geriatric ED of Hospital Sírio-Libanês, willing and able to give informed consent and with at least one of the following for indication and training of mobility aids: reduction of postural instability; improvement of motor control; increase of somatosensory feedback; reduction of biomechanical overload; safe promotion of autonomy; fall history (in the last six months). Exclusion criteria will include altered level of conscience, need for supplemental oxygen (≥3L/min), respiratory distress, hemodynamic instability, postural instability with a tendency to fall backward, cognitive impairment that limits the use of walking aids, hospitalization after ED evaluation, and delirium.

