### Data handling

Data used in this study will be collected and managed using the software *“Research Electronic Data Capture”* (REDCap) [12] hosted on the servers of the Hospital Sírio-Libanês. REDCap is a safe software web-based and designed to capture information, providing: 1) an intuitive interface for validated data collection; 2) audit trails for screening data manipulation and export procedures; 3) automated export procedures for continuous data downloads to common statistical packages; 4) procedures for importing data from external sources [12]. REDCap is a secure, browser-based web application widely used by researchers for survey data collection. REDCap offers unique features that can be used to conduct rigorous randomized controlled trials (RCTs).

Research assistants will have a tablet with online access to the study database through login and password to fill out the screening, application, and signature of the Informed Consent Term through the functionality of REDCap eConsent framework, and complete the assessment data during the project.

Data to be collected at baseline include age, sex, social and demographic parameters, clinical parameters, detailed medication history, functionality, cognition, quality of life, mobility in life spaces, gait speed, muscle strength, fear of falling, and fall history.

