Telemonitoring has been more frequently studied in older adults, but mainly in ambulatory settings and focused on chronic illnesses [48–50]. In this study, the intervention will be evaluated in acutely ill older patients admitted to a Geriatric ED and trained in the use of walking aids. In addition, in a randomized clinical trial, telemonitoring could be an additional strategy to reduce the loss of follow-up of participants during the study.

Finally, to the best of our knowledge, there are no previous studies that have compared groups according to the provision of gait assistance devices and used FES-I as a main outcomes. Therefore, we’ve calculated the sample size using as a reference the study by Morgan et al. [11] which proposed a gait assistance device intervention in its participants and had a higher reported DMC than other initiative [51] but conducted intragroup comparisons. In addition, our study will also address intragroup differences when comparing baseline, 3 and 6 months after discharge from the geriatric ED.

A limitation of the study protocol is that it will be performed in a single center. However, having been described in detail, registered in a public database, and published in an open-source journal, it might be replicated by other research groups around the globe. In addition, another limitation of the study is that participants in the control group may initiate the use of assistive gait devices over the 6-month study period. However, this identification will be possible through the LSA questionnaire. After completion of the study and blind analysis of the data by the statistician, the percentage of individuals in the control group who initiated the use of gait devices will be shown. If there are patients in the control group who initiated the use of a gait device, it will be considered a protocol deviation from the assessment point at which they started using the assistive gait device, which may be 3 or 6 months after discharge from the geriatric ED service. Consequently, a secondary analysis will be presented without the protocol deviation values.

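### The between-arm FES-I test ignores baseline FES-I and is chosen by a normality test, while change over time is tested only within arms; one baseline-adjusted model would be a free improvement

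*Protocol article*

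**What the plan says.** The Primary outcome section reads "The primary outcome will be fear of falling", and the Fear of falling section says it is measured by FES-I (range 16 to 64).

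The Statistical analysis section gives two families of test. Between arms: "For comparisons between groups over time, One-way ANOVA test for parametric data or Kruskall-Wallis for non-parametric data will be used". Within arms: "For intragroup analyses, repeated measures Analysis of Variance (RM-ANOVA) test for parametric data or Friedman test for non-parametric data will be used". The visits are the same for both: "For intergroup and intragroup analyses, the baseline, 3 and 6 months after discharge from the geriatric ED will be considered". Normality is checked by Shapiro-Wilk, and the parametric or rank test follows from that check. No baseline covariate, change score or arm-by-visit term is named.

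The baseline data listed under Data handling include "mobility in life spaces, gait speed, muscle strength, fear of falling, and fall history", and the Assessment moments section places the baseline assessment before randomisation. Every randomised participant should therefore have a baseline FES-I score. The Discussion adds that intragroup differences across baseline, 3 and 6 months will also be addressed.

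**The concern.** The article names its tests, visits and software, so this is a choice it has made and not a detail left to another document. Four features of that choice are weak.

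- One-way ANOVA and Kruskal-Wallis have no time factor, so the named test does not match its description as a comparison over time.
- A between-arm test at baseline, before any intervention, answers no efficacy question.
- The Shapiro-Wilk switch lets the data decide whether the primary comparison concerns means or ranks, and the answer could differ between 3 and 6 months.
- Baseline FES-I is collected but plays no part in the between-arm test.

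Two things are at stake. Precision is given up that would cost nothing to keep. Also, because time is modelled only within arms, a change that is significant in one arm and not in another may be taken for a treatment effect.

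**Working it through.** **Inputs.** From the Sample section: "minimal detectable change (MDC_95_) of 8,2 points on Falls Efficacy Scale International (FES-I), with a standard deviation of 12 points"; three groups; two-sided 5% level; power 0.80; 20% loss; 51 per arm. The article gives no baseline-to-follow-up correlation r for FES-I, so r = 0.3 to 0.6 is an assumption.

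**1. The plan's own figure.** The article says: "For an α of 0.05 and a power of 0.80, the total sample size was computed as 42 individuals". For a three-group one-way ANOVA with means 0, 4.1 and 8.2, the SD of the means is 3.348, so f = 3.348/12 = 0.279. The noncentral F distribution with noncentrality f² × 3n gives power 0.797 at n = 42 per arm and 0.807 at 43. The figure is thus reproduced if 42 is per arm; then 42 × 1.2 = 50.4, rounded up to 51 per arm and 153 in total. Read as a total (14 per arm), power would be 0.32. That labelling is a separate matter.

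**2. Power with and without baseline.** Expected completers are 51 × 0.8 = 40.8, about 41 per arm. Adjusting for baseline multiplies the residual variance by (1 − r²), so f becomes 0.279/√(1 − r²).

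| r (assumed) | 1 − r² | f | power at 41 per arm |
|---|---|---|---|
| unadjusted | 1.00 | 0.279 | 0.787 |
| 0.3 | 0.91 | 0.292 | 0.826 |
| 0.4 | 0.84 | 0.304 | 0.856 |
| 0.5 | 0.75 | 0.322 | 0.895 |
| 0.6 | 0.64 | 0.349 | 0.938 |

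The pattern of means matters. If one arm differs by 8.2 from two equal arms, f = 0.322. Unadjusted power at 41 per arm is then already 0.895, and adjustment gives 0.922 to 0.983 over the same range of r.

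**3. Validity of the unadjusted test.** In 4,000 simulated trials per setting, with no arm difference, 40 per arm and r of 0.5 or 0.7, the one-way ANOVA at a follow-up visit rejected in 0.045 to 0.053 of trials. Its error rate per visit is correct.

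**4. Within-arm tests when the arms do not differ.** Let every arm change by d within-person SDs, and let p be the power of a paired test in one arm at n = 41. The chance that the three arms do not all agree on significance is 1 − p³ − (1 − p)³.

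| d | p | chance of disagreement |
|---|---|---|
| 0 | 0.050 | 14% |
| 0.1 | 0.096 | 26% |
| 0.2 | 0.240 | 55% |
| 0.3 | 0.466 | 75% |
| 0.5 | 0.878 | 32% |
| 0.68 | 0.989 | 3% |

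The formula peaks at 75% when p = 0.5, so d = 0.3 is close to the worst case. The same simulations, run with the RM-ANOVA that the plan names, agree. Disagreement is 14% to 15% with no change, 44% to 75% when every arm improves by 2 to 4 points, and 3% to 25% when every arm improves by 6 points.

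**The case against.** The strongest reply is that the plan already has a sound primary comparison. Randomised arms share the same expected baseline, so the difference in follow-up FES-I has the same expectation as the difference in change. The trial was also sized on a three-group ANOVA, so the planned test and the powered test agree. This stands, and it rules out several stronger readings.

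- A reader might infer that the plan never tests whether the arms change differently, or that it abandons the randomised comparison. Neither follows. The between-arm test is stated first, at the same visits as the within-arm test. The article also does not say whether the dependent variable is the score or its change. An ANOVA of change scores would still not outperform baseline adjustment: at 40 per arm and r = 0.5, power is 0.776 for change against 0.887 adjusted.
- A reader might infer that anyone with a missing visit is dropped. Classical RM-ANOVA and Friedman do need complete rows, but those are the within-arm tests. A one-way ANOVA at a visit loses only those absent at that visit, and a missing-data rule may sit in a plan not shown.
- A reader might infer a bias from unequal loss, because the Discussion says "telemonitoring could be an additional strategy to reduce the loss of follow-up of participants during the study" and only one arm receives telemonitoring. The article gives no arm-specific loss and says only that this could happen. Any bias expressed in points would rest on invented inputs, and a baseline-adjusted model would not fully remove it.
- A reader might infer that within-arm significance will be offered as proof of efficacy. The article presents the intragroup analyses as additional and does not say this. The risk lies in how the results may be read.

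What the reply leaves untouched is the unused baseline score, the baseline test, the data-driven choice of test, and the lack of a stated role for the within-arm results.

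**Conclusion.** The point holds as a free improvement. The between-arm test at follow-up is valid but less precise than it need be. Under the article's difference and SD, with evenly spaced means and 41 completers per arm, power is 0.787, just under the planned 0.80. Baseline adjustment raises it to between 0.826 and 0.938 for assumed correlations of 0.3 to 0.6; the size of the gain depends on that unstated correlation and on the pattern of means. The within-arm tests cannot carry an efficacy conclusion: with equal change in all arms they disagree in roughly 3% to 75% of trials, and in 14% when nothing changes at all. The baseline comparison and the Shapiro-Wilk switch add nothing to the efficacy question and leave the primary analysis open to the data.

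**What to change.** Name one baseline-adjusted between-arm model for FES-I as the primary analysis. Either of these is enough:

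- ANCOVA of FES-I at a named visit, with arm and baseline FES-I; or
- a linear mixed model of 3- and 6-month FES-I, with arm, visit, arm-by-visit and baseline FES-I.

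Report adjusted differences between arms with 95% CIs. Remove the between-arm significance test at baseline, and do not let Shapiro-Wilk select the test. Keep the within-arm analyses if wanted, labelled descriptive.

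The cost is a few sentences in the Statistical analysis section. The data collected, the sample size and the software (SPSS) do not change.
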